**6.1.3.3. Follow-up for toxicity**

In case of temporary or permanent therapy discontinuation, the patient should be followed up until the resolution or stabilization of the event. If the therapy is suspended for more than 14 days, it should be discontinued permanently. However, if the investigator and the CRA believe that the patient who discontinued adalimumab for more than 14 days may get benefit from the therapy, **adalimumab treatment can be continued.**

To detect AEs and SAEs, all patients will be followed up for 28 days from the last dose of BCD-057/Humira®.

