#### ***4.8.2. Criteria for premature withdrawal of study subjects***

The patient will be withdrawn from the study in the following circumstances:

1. A major violation of inclusion/exclusion criteria is revealed after the patient was enrolled in the study (withdrawn by the decision of JSC BIOCAD).
2. The patient recalls his/her consent to participate in the study.
3. The patient develops adverse events or serious adverse events, laboratory abnormalities or comorbidities that, in the investigator's opinion, make further participation in the study

---

 Deviations from inclusion/exclusion criteria justified by the investigator and approved by the Sponsor are not considered a reason for withdrawal.

impossible, dangerous or non-beneficial regarding patient's well-being and/or safety.

4. The patient misses more than 4 injections and/or visits during the study (compliance < 85%) or misses 2 consecutive injections and/or visits, or breaches the specified time windows for more than 5 visits.
5. The patient develops active tuberculosis. If the patient has indeterminant or positive results of the QuantiFERON assay or T-Spot.TB or Diaskintest® at Week 25, he/she can continue the study only if all three of the following requirements are met:
  - The patient tests negative in one additional QuantiFERON / T-Spot.TB assay.
  - The chest X-ray shows no signs of active tuberculosis.
  - The TB specialist confirms that the patient has no tuberculosis.Otherwise, the patient has to be removed from the study.
6. The patient gets pregnant. If pregnancy is suspected, the urine test for HCG must be performed. If the test gives a positive result, the patient must be withdrawn from the study (follow-up procedures are described in section 5.4).
7. The patient has a major depressive disorder or suicidal ideation or makes suicidal attempts.
8. The study is terminated by JSC BIOCAD, local ethics committees, or regulatory authorities.
9. The patient uses medications prohibited by the Protocol.
10. The patient dies.

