### 5.3. *Withdrawal criteria*

The patient will be withdrawn from the study in the following circumstances:

1. Major violations of inclusion and/or exclusion criteria revealed after the enrollment (patients removed at the discretion of JSC BIOCAD).
2. The patient recalls his/her consent to participate in the study.
3. The patient develops adverse events or serious adverse events, laboratory abnormalities or comorbidities that, in the investigator's opinion, make further participation in the study impossible, dangerous or non-beneficial regarding patient's well-being and/or safety.
4. The patient misses more than 4 injections and/or visits during the study (compliance < 85%) or misses 2 consecutive injections and/or visits, or breaches the specified time windows for more than 5 visits.
5. The patient develops active tuberculosis. If the patient has indeterminant or positive results of the QuantiFERON assay or T-Spot.TB or Diasptest® at Week 25, he/she can continue the study only if all three of the following requirements are met:

---

 Patients whose screening was interrupted due to force majeure circumstances (external events beyond the patient's and investigator's control) could be re-screened in this study.

 Deviations from inclusion and/or exclusion criteria justified by the investigator and approved by the Sponsor are not considered a reason for withdrawal.

- The patient tests negative in one additional QuantiFERON / T-Spot.TB assay.
  - The chest X-ray shows no signs of active tuberculosis.
  - The TB specialist confirms that the patient has no tuberculosis.
  - Otherwise, the patient has to be removed from the study.
6. The patient gets pregnant. If pregnancy is suspected, the urine test for HCG must be performed. If the test gives a positive result, the patient must be withdrawn from the study (follow-up procedures are described in section 5.4).
  7. The patient has a major depressive disorder or suicidal ideation or makes suicidal attempts.
  8. The study is terminated by the decision of JSC BIOCAD, local ethics committees or regulatory authorities.
  9. The patient used medications prohibited by the Protocol.
  10. The patient dies.

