### ***6.1.3. Adjustment and discontinuation of study therapy***

#### ***6.1.3.1. Dose modification and discontinuation for the test or reference drug***

No dose modifications are allowed either for BCD-057 or Humira®. The patients should not compensate for missed doses of BCD-057/Humira® (e.g. the patient should not double the next dose of BCD-057/Humira® if he/she have missed the previous one).

During the treatment with adalimumab, the following events have been reported: infections (including tuberculosis and reactivation of hepatitis B), neurological disorders in patients with demyelinating diseases of the CNS, malignancies, allergies, hematological complications (including pancytopenia and aplastic anemia), lupus-like syndrome, and allergic reactions. Adalimumab should be discontinued if the patient develops a serious infection or sepsis, tuberculosis, a severe fungal infection, symptoms suggesting a demyelinating disease, a malignancy, serious allergic reactions, significant blood abnormalities, severe CHF and/or symptoms of lupus-like syndrome.

The investigator decides whether to discontinue the therapy (temporarily or permanently) taking into account the patient's complaints and general health state, physical exam results, laboratory values, and other factors indicating that continuation of the study therapy is not possible, dangerous to the patient or does not benefit the patient's well-being and safety.

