#### ***6.1.3.2. Acceptable changes in visit schedule***

##### ***All patients***

In the case of adverse events - for not more than 14 days. If the AE does not resolve in 14 days and, in the investigator's opinion, poses the risk to patient's health, the patient has to be withdrawn from the study. However, if the investigator and the CRA believe that the patient who discontinued adalimumab for more than 14 days may get benefit from the therapy, **adalimumab treatment can be continued.**

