### ***11.3. Investigator's responsibility to comply with the Protocol***

At each study site, the decision regarding patient's early withdrawal from the study has to be approved by JSC BIOCAD.

If the investigator decides to withdraw a patient from the study, he/she must send a request, specifying a reason for withdrawal, to BIOCAD's Medical Advisory Division by [contact]. Within 48 hours (except for weekends and public holidays) from the time when the request was received by the Medical Advisory Department, JSC BIOCAD should notify the investigator of the decision regarding patient withdrawal. If a patient has to be immediately withdrawn from the study due to an SAE, the investigator must inform JSC BIOCAD about the SAE within 24 hours but does not have to wait for approval from JSC BIOCAD.

If a subject does not attend a scheduled visit or makes unauthorized changes in the dose of the investigational product, the investigator must report the violation to the Medical Advisory Division

of JSC BIOCAD within 24 hours from the time of awareness (by fax: [name]). Medical advisors will instruct the investigator on further case management and on how to document the causes of the violations in the CRF/source documents.

If the investigator fails to follow these procedures or if multiple Protocol violations occur, JSC BIOCAD may suspend or terminate the study at this particular study site.

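### Adalimumab may be continued after an adverse-event hold of more than 14 days if the investigator and the CRA agree, with no sponsor medical approval, no need for the event to have resolved and no stated exclusion of the Section 6.1.3.1 events

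*Protocol*

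**What the plan says.** Three parts of Protocol Section 6.1.3 bear on this.

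- **6.1.3.1** lists the events that call for stopping: "Adalimumab should be discontinued if the patient develops a serious infection or sepsis, tuberculosis, a severe fungal infection", and then "symptoms suggesting a demyelinating disease, a malignancy, serious allergic reactions, significant blood abnormalities, severe CHF and/or symptoms of lupus-like syndrome". It goes on to leave the choice between a temporary and a permanent stop to the investigator, who is to weigh complaints, general health, examination findings and laboratory values.
- **6.1.3.2**, under the heading for all patients, caps a delay for an adverse event at 14 days. For an event that is unresolved by then and that the investigator considers harmful, the rule and its exception run together: "poses the risk to patient's health, the patient has to be withdrawn from the study. However, if the investigator and the CRA believe". The exception is that treatment may go on if both think the patient may benefit.
- **6.1.3.3** covers temporary and permanent discontinuation alike. It makes a suspension of more than 14 days permanent, then adds the same exception: "if the investigator and the CRA believe that the patient who discontinued adalimumab for more than 14 days may get benefit from the therapy".

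The withdrawal criteria in 4.8.2 and 5.3 name one of the 6.1.3.1 events outright: "The patient develops active tuberculosis". Criterion 3 covers adverse events that, "in the investigator's opinion, make further participation in the study impossible, dangerous or non-beneficial".

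On decision-makers, Section 11.4 describes the CRA as a representative of the sponsor or a CRO who checks records, CRF accuracy, protocol and GCP adherence, recruitment and drug accounting. Section 11.3 says that at each site "the decision regarding patient's early withdrawal from the study has to be approved by JSC BIOCAD", with requests going to the Medical Advisory Division. An urgent withdrawal for an SAE need not wait for that approval.

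**The concern.** The 14-day limit is the protocol's only fixed brake on resuming a TNF blocker after an adverse event. The exception releases it on a belief in possible benefit, and in 6.1.3.2 it does so immediately after the case in which the event is still present and judged a risk. The second signatory is the site monitor, whose stated tasks are not medical.

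What is at stake is the safety of individual patients. Read as written, the exception could be applied to someone with a serious infection or a new malignancy, without the event having resolved and without a sponsor physician agreeing. The same protocol excludes severe heart failure, demyelinating disease and malignancy in remission for less than 5 years at entry, and Section 1.4.2 gives risk reduction as the reason. It would be inconsistent to leave re-dosing after such an event on study less controlled than entry.

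**Working it through.** The plan gives no figure to reproduce, so the check is a comparison of provisions.

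**1. What the exception requires.** Both sections ask for one thing: that the investigator and the CRA believe the patient may benefit. Neither mentions resolution, grade, type of event, a maximum length of hold, or a sponsor physician.

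**2. Whether it reaches the 6.1.3.1 events.** 6.1.3.1 speaks of discontinuing adalimumab and allows that to be temporary. 6.1.3.3 opens with temporary or permanent discontinuation. The exception covers a patient who has discontinued for more than 14 days and removes no event from its scope. The listed events therefore fall within the wording, although no sentence expressly permits a restart after them.

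**3. What else could stop a restart.**

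- Active tuberculosis: withdrawal criterion 5. This is a firm bar.
- Criterion 3: withdrawal is required if the investigator considers continuation dangerous. This is a real limit, but it rests on the judgement of the same person who applies the exception.
- Section 6.2.2 and criterion 9: a patient who needs systemic glucocorticoids, methotrexate, cyclophosphamide or another listed agent must be withdrawn. Treatment of some 6.1.3.1 events may trigger this, but not of all.
- SAE reporting (8.2.2, 12.1): the sponsor is told within 24 hours and analyses the report. Nothing ties that review to the decision to resume.
- Missed-visit reporting (11.3): medical advisors direct case management. This applies only when a scheduled visit is not attended.
- Criterion 4: two consecutive missed injections lead to withdrawal. Maintenance doses are 14 days apart, so on a fixed calendar a dose held for more than 14 days also passes the next one. The re-dating paragraph in 6.1.3.2 would instead move later visits, but it sits under the PK heading and names only BCD-057. The text does not say whether a held dose counts as missed or postponed.

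None of these makes sponsor medical approval a condition of restarting.

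**4. Who signs comparable decisions.**

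| Decision | Sign-off |
|---|---|
| Withdrawing a patient (11.3) | Sponsor, through the Medical Advisory Division |
| Emergency unblinding (4.10) | Sponsor's medical expert, pharmacovigilance officer or study manager |
| Delay beyond 7 days for non-treatment reasons (6.1.3.2: patients outside the PK study; PK patients from Week 24) | Sponsor |
| Dosing again after an adverse-event hold of more than 14 days (6.1.3.2, 6.1.3.3) | Investigator and CRA |

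The last row carries the most direct medical risk and is the only one with no sponsor medical or sponsor-level approval.

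**5. Whether the number of restarts can be estimated.** Exposure, assuming full follow-up, is 344 × 51/52 = 337.4 patient-years. For serious infections without tuberculosis:

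- Section 1.3.2.3 (M03-656, Period C, figures read as rates per patient-year, which is an assumption): 337.4 × (0.020 − 0.002) = 6.1.
- Section 1.4.2 (studies not limited to psoriasis): 337.4 × (0.046 − 0.0022) = 14.8.

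These are background events. The protocol gives no share that would be held for more than 14 days and put forward for restart. A purely assumed share of 10% to 50% gives 6.07 × 0.1 = 0.6 to 14.78 × 0.5 = 7.4. That roughly twelvefold range comes largely from the assumption, so it is not an estimate.

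**The case against.** The strongest reply is that 6.1.3.1 is a specific rule for named events while the exception is a general rule about the length of a hold, so the specific rule still binds. On that reading, nothing permits re-dosing after, say, a malignancy. 6.1.3.1 also tells the investigator what to weigh, and criterion 3 compels withdrawal once continuation is judged dangerous. A belief in benefit therefore never stands wholly alone.

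Much of this is right. A reader might infer that the protocol authorises restarts after 6.1.3.1 events with no criteria at all, or that tuberculosis is the only event for which any safeguard exists. The documents do not support either reading: the reach to those events is an inference from unrestricted wording, and the partial limits set out above are real.

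What stands is narrower. The specific-rule reading is reasonable but unstated, and 6.1.3.1 itself allows a temporary stop, so it does not settle what happens afterwards. The remaining safeguards depend on the investigator or on circumstances that may not arise, such as a missed visit or a need for prohibited medication. The choice of the CRA as co-decider is not a matter of interpretation.

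It is also fair to say that resuming after some listed events, such as a resolved serious infection, can be sound practice. The point is who approves it and on what condition.

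**Conclusion.** The point holds as a fault in a stated safety rule. The exception in 6.1.3.2 and 6.1.3.3 gives a medical decision to the investigator and a monitor, does not require the event to have resolved, and does not say that the 6.1.3.1 events are outside it. The missing conditions and the CRA's role are plain on the text. That restarts after 6.1.3.1 events are allowed is a possible reading and not an express permission.

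The number of restarts affected is unknown and probably small. A reader might take the background event rates as a count of unsafe restarts; the protocol gives no basis for that step. There is no material effect on the Week 16 PASI 75 comparison, the sample size or the equivalence test. The case for changing the text rests on the seriousness of a single wrong restart and the low cost of preventing it.

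**What to change.** In both 6.1.3.2 and 6.1.3.3:

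1. Replace the CRA with the sponsor's Medical Advisory Division, which already decides withdrawal requests under 11.3.
2. Require that the adverse event has resolved or stabilised and is no longer judged a risk to the patient.
3. State that the exception does not apply to the events listed in 6.1.3.1, unless the sponsor's clinicians have named an event there as resumable after resolution.

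The cost is amendment wording, a notice to sites and monitors, and a short wait for sign-off; the 48-hour response time in 11.3 could be reused. Visits, sample size and analysis are unchanged.

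A separate, minor clarification could go in the same amendment: move the re-dating paragraph of 6.1.3.2 to the text for all patients, name both products, and say whether a dose held for an adverse event counts as postponed or missed under withdrawal criterion 4.

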**6.1.4. Overdose**

**6.1.4.1. Overdose with the test drug and/or the reference drug**

The maximum tolerable dose of adalimumab in humans has not been established. Multiple doses of up to 10 mg/kg did not produce any toxicity that would require dose reduction. No specific antidote is available to adalimumab.

In case of an overdose, the subject should be monitored for any toxicity signs. If any toxicity signs are observed, standard symptomatic therapy should be administered.

**6.2. Concomitant therapy, medications allowed and prohibited by the Protocol**

**6.2.1. Allowed concomitant therapy**

Study subjects should tell the study team about any new medications that they have received after the initiation of the study therapy. All medications (except for BCD-057/Humira®) and significant non-medication therapies (including physical therapy, herbal medicines/agents of natural origin, and blood transfusion) used during the study had to be documented in the CRF (sections *Concomitant Therapy* and/or *Surgery or Other Medical Procedures*).

Study subjects may take any medications that are not prohibited by the Protocol.

Patients are allowed to use topical moisturizers, emollients, oils, salicylic acid products, topical antibacterial and antimycotic agents, and topical glucocorticoids as needed. All patients must discontinue all topical skin products (medications or cosmetics) 24 hours before the planned PASI assessment.

If the patient has been using any allowed concomitant therapy, he/she has to continue it at the same dose and regimen throughout the entire study (if reasonable from the medical point of view). On days when PK blood samples are taken (in a limited population), the patient has to continue the usual regimen of his/her concomitant therapy. However, if the patient uses occasionally any concomitant medication during the study, he/she will be requested to avoid it on the days of blood sampling, if possible.

### ***6.2.2. Prohibited concomitant therapy***

Treatments prohibited in this study:

- Phototherapy (including selective phototherapy (UVB) and PUVA).
- Systemic glucocorticoids (oral or parenteral glucocorticoids are prohibited regardless of the indication).
- Genetically engineered biological medicinal products (tumor necrosis factor alpha blockers, anti-cytokine agents, etc.).
- Systemic non-biological anti-inflammatory agents (methotrexate, sulfasalazine, chlorambucil, leflunomide, cyclosporine A, azathioprine, cyclophosphamide, cyclosporine, apremilast, mycophenolate mofetil, etc.).
- Aromatic retinoids (acitretin).
- Live or attenuated vaccines.

If, in the investigator's opinion, the patient needs any of the medications listed above, the patient has to be withdrawn from the study before the initiation of prohibited therapy.

### ***6.3. Compliance***

The patient is considered non-compliant if he/she misses more than 4 injections and/or visits during the study (compliance < 85%) or misses 2 consecutive injections and/or visits or breaches the specified time windows for more than 5 visits. Patients are not allowed to miss the first blood sampling.

---

 The Protocol allows single doses of systemic glucocorticoids to manage acute anaphylactic reactions, shock or other life-threatening events that developed as adverse events in patients during the study.

## **7. Efficacy evaluation**

### **7.1. List of efficacy variables**

#### **7.1.1. Definition of variables**

The efficacy will be assessed based on the indicators of the disease activity and patient's general health.

The PASI is a commonly used tool to assess the area and severity of psoriasis in clinical trials. The PASI score is an integral value from 0 (no symptoms) to 72 (the most severe psoriatic process). It shows the area affected by psoriasis (on the head, legs, arms, and trunk) and includes the severity of erythema, scaling, and induration. There are several modifications of PASI scoring, but the most conventional one is a scale considering all the three signs given above. The information value of the method decreases if the body surface area affected by psoriasis is too small.

The PGA scale is another common tool used to assess the severity of psoriasis. The scale includes 5, 6, or 7 items that the investigator uses to assess the severity of the disease. In most versions of the PGA scale, the morphology of plaques and the area of skin affected by psoriasis are not taken into account. This makes the assessment rather intuitive. The PGA score 0 refers to no signs of psoriasis, while the maximum score refers to the highest disease severity. This scale has several modifications, and the sPGA (static PGA) is the most commonly used one. The sPGA scale allows assessing psoriasis signs at a certain time point. The dPGA (dynamic PGA) scale can be also used in clinical studies. However, when using the dPGA, the physician should remember how he/she assessed the severity of psoriasis during the previous assessment, and this is not always possible. This study uses the sPGA scale consisting of 5 questions.

The body surface area (BSA) affected by psoriasis is another conventional endpoint used in clinical studies. This measure allows an objective assessment of the extent of psoriasis.

This study also evaluates the health-related quality of life. The SF-36 is a standard validated and commonly used questionnaire to assess this parameter. The DLQI questionnaire allows specifically assessing the quality of life in patients with skin diseases.

#### **7.1.2. Efficacy endpoints**

##### ***Primary endpoint:***

- The proportion of patients with a 75% or greater PASI improvement (reduction) from baseline (PASI 75) at Week 16.

##### ***Secondary endpoints:***

- Changes from baseline in PASI (%) at weeks 16, 24, 33, and 55, by study arms.
- The proportion of patients with a 75% reduction from baseline in psoriasis area and severity (PASI 75 response) at weeks 24, 33, and 55.
- The proportion of patients with a 50% and 90% PASI reduction from baseline at weeks 16, 24, 33, and 55.
- The proportion of patients with sPGA score reduced to 0 (complete clearance) or 1 (minimal disease) at weeks 16, 24, 33, and 55.
- Changes from baseline in affected BSA (%) at weeks 16, 24, 33, and 55.
- Changes from baseline in NAPSI (%) at weeks 16, 24, 33, and 55.
- Change from baseline in the itch severity (VAS score from 0 to 100) at weeks 16, 24, 33, and 55.
- Changes from baseline in health-related quality of life (DLQI and SF-36 scores) at weeks 16, 24, 33, and 55.

